### 8.2.3. Assessment of Causality

The relationship between each adverse event and the investigational device, the comparator and the investigation procedure will be assessed and recorded by the investigator and sponsor. For assessment of causality, the IB and the risk analysis report will be consulted. The sponsor and investigator will distinguish between SAEs related to the investigational device and those related to the procedures, relatedness to both is possible.

Each SAE will be classified according to four different levels of causality:

#### 1. Not related

Relationship to the device or procedures can be excluded when:

- the event has no temporal relationship with the use of the investigational device, or the procedures related to application of the investigational device;
- the SAE does not follow a known response pattern to the medical device (if the response pattern is previously known) and is biologically implausible;
- the discontinuation of medical device application or the reduction of the level of activation/exposure - when clinically feasible - and reintroduction of its use (or increase of the level of activation/exposure), do not impact on the serious adverse event;
- the event involves a body-site or an organ that cannot be affected by the device or procedure;
- the SAE can be attributed to another cause (e.g., an underlying or concurrent illness/ clinical condition, an effect of another device, drug, treatment or other risk factors);
- the event does not depend on a false result given by the investigational device used for diagnosis, when applicable;

In order to establish the non-relatedness, not all the criteria listed above might be met at the same time, depending on the type of device/procedures and the SAE.

#### 2. Possible

The relationship with the use of the investigational device or the relationship with procedures is weak but cannot be ruled out completely. Alternative causes are also

possible (e.g., an underlying or concurrent illness/ clinical condition or/and an effect of another device, drug or treatment). Cases where relatedness cannot be assessed, or no information has been obtained should also be classified as possible.

3. Probable

The relationship with the use of the investigational device or the relationship with procedures seems relevant and/or the event cannot be reasonably explained by another cause.

4. Causal relationship

The SAE is associated with the investigational device or with procedures beyond reasonable doubt when:

- the event is a known side effect of the product category the device belongs to or of similar devices and procedures;
- the event has a temporal relationship with investigational device use/application or procedures;
- the event involves a body-site or organ that
  - o the investigational device or procedures are applied to;
  - o the investigational device or procedures have an effect on;
- the serious adverse event follows a known response pattern to the medical device (if the response pattern is previously known);
- the discontinuation of medical device application (or reduction of the level of activation/exposure) and reintroduction of its use (or increase of the level of activation/exposure), impact on the SAE (when clinically feasible);
- other possible causes (e.g., an underlying or concurrent illness/ clinical condition or/and an effect of another device, drug or treatment) have been adequately ruled out;
- harm to the subject is due to error in use

In order to establish the relatedness, not all the criteria listed above might be met at the same time, depending on the type of device/procedures and the SAE.

### 8.3. List of foreseeable Adverse events

Vertigo, nausea or mild discomfort during the vestibular rehabilitation, regardless of randomization allocation. These symptoms are common after acute vertigo and during vestibular rehabilitation and all subjects are expected to develop such symptoms. Weekly evaluations of these symptoms are included in the online tool and the training intensity is automatically tailored based on symptom intensity. For those randomized to standard care, instructions on lowering training intensity in case of severe discomfort will be given together with the training instructions. The test circumstances at the sites will be designed to provide a safe environment ensuring that no participant will lose balance and fall during walking test.

## 8.4. Follow-up of adverse events

Serious adverse events and adverse events with a causal relationship to the device that are ongoing at study end will be followed at the site where the participant is registered until the adverse event is either resolved, stable, or persistent. In case of unacceptable adverse events, necessary measures will be taken.

Adverse events and serious adverse events without causal relationship to the device will be followed as part of routine care within the health care system. If necessary the site PI is responsible for notifying the corresponding party responsible for follow up.

## 9. Statistical considerations

### 9.1. Analysis population

The primary analysis will be performed using the intention to treat cohort on both primary and secondary outcomes. Per protocol analyses will also be performed as part of the sensitivity analysis.

### 9.2. Descriptive statistics

Baseline characteristics in both arms will be described using descriptive statistics. The two study arms will be described and compared at baseline using a table including relevant baseline variables. In accordance with the CONSORT protocol no statistical tests of the baseline values will be performed.

### 9.3. Analytical procedures

Two-sided statistical tests will always be performed. The primary outcome will be analyzed using analysis of covariance (ANCOVA) adjusting for baseline measurements; known predictors of the outcome including diagnostic group, sex, age and baseline symptom intensity in order to gain precision in treatment effect estimates; and inclusion of a random effect for site to control for influence from stratified randomization. The primary endpoint results will be reported as the ANCOVA generated adjusted VSS-SF difference with 95% CI and p-value between the study arms at 6 weeks. The VSS-SF has previously been analyzed in a randomized trial assuming normality. If a clear deviation from normality is detected an ordinal logistic regression ANCOVA will be used for the primary outcome.

For secondary outcomes with repeated measurements we will use linear mixed models analysis for continuous outcome variables and binary logistic mixed effects models for binary outcome variables with random effects for individual and site. These techniques can account for repeated measures within an individual and unbalances from missing data. The intervention effect will be modelled using a time by intervention interaction term.

We will also perform statistical validation of the Swedish translation of the VSS-SF questionnaire, including analyses of reliability (test-retest reliability and internal consistency reliability) and validity; construct validity (convergent and discriminant validity) by investigating item-to-item associations between VSS-SF/VSS-SF domains and DHI; and criterion validity by correlating the domains to DHI and balance tests. For the test-retest

study, the first 100 included subjects will complete the evaluator-blinded 6-week assessments of VSS-SF twice, 48 hours apart, via telephone .

Ranked analysis of covariance (ANCOVA) will be used to evaluate intervention effects on T25-FW and VOR gain and saccades, as this method provides robust estimates even though there may be extreme outliers in skewed data. The percentage of participants with sustained improvement in VSS-SF defined as  $\geq 3$  points improvement at 6 weeks and 3 months will also be compared using binary logistic regression.

We will report crude and adjusted analyses, adjusting for baseline values of the studied outcome and the prespecified predictors sex, age, level of education, number of chronic diseases and baseline AVS etiology.

Please refer to the schedule of events below for an overview of data collection by time points. Statistician [name], Registercentrum Norr, will be responsible for the statistical analysis plan.

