## 6.3. Measurement of variables

The VSS-SF measures the frequency of 15 vestibular symptoms on a scale from 0 (no symptoms) to 4 (symptoms most days) during the past month. The score range is 0–60 and a difference from baseline of  $\geq 3$  points indicate a clinically significant change. The time frame (1 month) for the symptoms will be left as is for the evaluations at week 6 and after 3 months but for the baseline measurement the participants will be asked to report their symptoms during the last 24 hours; and the two response alternatives indicating the highest frequencies (3, quite often [every week] and 4, very often [almost every day]) will be modified to: 3, quite often (almost every hour) and 4, very often (almost all the time). Although this is a deviation from the original version of the VSS-SF this modification is necessary to capture the short-term status of participants soon after vertigo onset. The modified VSS-SF data will be used for the baseline symptom intensity assessments only.

The DHI (range 0–100 points, 0–30 mild, 31–60 moderate and  $\geq 61$  severe dizziness) investigates the effects of dizziness on everyday living. The between group mean DHI score will be compared at each time point as detailed in the statistics section. The scale has subcategories (physical, emotional and functional for DHI) and these will be analyzed separately as exploratory analyses although the total scores will be used for the secondary outcomes.

EQ-5D is an generic instrument which consists of five sub-domains (mobility, self-care, usual activities, pain/discomfort and anxiety/depression) with three severity levels (no, moderate and severe problems). For the current study, the Swedish version EQ-5D-3L will be applied, and the Swedish value set based on experienced health states will be applied to

obtain a health utility score in order to calculate quality-adjusted life years (QALYs). The UK MvH value set will be applied for sensitivity analyses.

The T25-FW data will be collected by using the mean (seconds) of two, timed attempts at walking a clearly marked 25-foot course.

Basic body sway data will be collected by using a locally developed application which utilizes cell phone built-in motion tracking. An enhanced gait analysis with a wearable motion tracking system will be performed at Umeå University Hospital for in-depth measurements.

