## 6.6. Subjects

### 6.6.1. Inclusion criteria

To be included in the study, subjects must meet the following criteria:

- $\geq 18$  years old; *and*
- The subject has given written consent to participate in the study; *and*
- New acute onset dizziness or vertigo since  $\geq 24$  hours with pathological spontaneous or gaze-evoked nystagmus (i.e., an acute vestibular syndrome, AVS). The nystagmus as described above must be present at investigation between 24 hours and 7 days from onset, spontaneously, gaze-evoked or head-shake evoked and documented; *and*
- Screening and inclusion within 7 days of onset of continuous symptoms; *and*
- Symptomatic at inclusion

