#### 9.4. Sample size calculation

A change in VSS-SF score of 3 or more has been defined as clinically significant. In an earlier study on a Dutch version of the online vestibular rehabilitation tool on primary care chronic dizziness patients the mean VSS-SF score at three months in the intervention group was 8.1 (SD 7.4), and in the control group 11.5 (SD 9.9). In order to detect a difference in VSS-SF score of 3, assuming a standard deviation of 9 and a correlation between pre and post measurements of 0.6 with 90% power, alpha 5%, we would need n=156 participants, 78 in each arm, using the Shieh sample size calculation method implemented into the Superpower package. Assuming a 15% drop out rate the sample size needs to be increased to n=184 to preserve power. Conservative observational data suggest a yearly incidence of 36 patients with acute onset vertigo and nystagmus per 100,000 inhabitants in the Umeå University uptake area.

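### Optional gain in precision: days from vertigo onset to baseline could be named as a covariate in the primary ANCOVA

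*Protocol*

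**What the plan says.** - **Covariates (9.3).** The primary model adjusts for baseline measurements and for "known predictors of the outcome including diagnostic group, sex, age and baseline symptom intensity in order to gain precision", with a random effect for site. A later list in the same section, for crude and adjusted analyses, has sex, age, education, number of chronic diseases and baseline etiology. Neither list names time since onset.
- **Entry window (6.6.1).** Nystagmus must be documented between 24 hours and 7 days from onset, and the criteria require "Screening and inclusion within 7 days of onset of continuous symptoms". Participants must also be symptomatic at inclusion.
- **Baseline score (6.3).** The VSS-SF normally asks about the past month, but "for the baseline measurement the participants will be asked to report their symptoms during the last 24 hours", with the two highest response options reworded. This version serves only to measure baseline intensity.
- **Outcome timing (5.2 and Table 1).** The primary endpoint is the VSS-SF at 6 weeks after vertigo onset. Table 1 places the contact at day 42 ± 3, with day 0 the baseline and randomization contact.
- **Sample size (9.4).** The calculation relies on "a correlation between pre and post measurements of 0.6".

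**The concern.** In an illness expected to improve over days, a 24-hour score taken on day 1 need not mean the same as an equal score taken on day 7. The model adjusts for the score but not for when it was taken. If the score falls over the entry window, variation in entry day acts as noise in the covariate and weakens the baseline–outcome correlation that the adjustment is meant to exploit.

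Entry day also moves the outcome. At the target day of 42 from baseline, the assessment falls 43 to 49 days after onset for entry on days 1 to 7, before the ± 3 day window is added.

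What is at stake is the precision of the primary difference, which is the stated purpose of the covariate adjustment.

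**Working it through.** **1. The plan's own figure.** Inputs from 9.3 and 9.4: "Two-sided statistical tests will always be performed"; "with 90% power, alpha 5" per cent; "In order to detect a difference in VSS-SF score of 3"; "assuming a standard deviation of 9"; "a correlation between pre and post measurements of 0.6"; 78 per arm.

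- With correlation 0.6, R² = 0.36 and the residual SD is 9 × √(1 − 0.36) = 7.2.
- The required number is 122 per arm by the normal approximation, or 123 by the exact random-covariate ANCOVA method. Exact power at 78 per arm is 0.731.
- The stated 78 per arm is reproduced (power 0.903) only if 0.6 is read as R². This is a separate matter that entry day neither causes nor repairs. It is noted because 0.731 is the reference value below.
- The dropout step reproduces: 156/0.85 = 183.5, rounded up to 184.

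**2. Effect of leaving out entry day.** Assumptions not given in the protocol:

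- entry is uniform over days 1 to 7, so its variance is 6²/12 = 3;
- the baseline SD is 9 and the correlation 0.6 at a fixed day;
- the 24-hour score falls linearly by k points per day;
- entry day is unrelated to the 6-week score given true severity.

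The baseline variance then grows from 81 to 81 + 3k², so R² without entry day = 0.36 × 81/(81 + 3k²). The residual variance ratio is (1 − R²)/0.64, and the equivalent loss of participants is 156 − 156/ratio.

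| k (points per day) | R² without day | Variance ratio | Like losing, of 156 | Exact power at 78 per arm |
|---|---|---|---|---|
| 0 | 0.360 | 1.000 | 0 | 0.731 |
| 1 | 0.347 | 1.020 | 3 | 0.723 |
| 2 | 0.314 | 1.073 | 11 | 0.701 |
| 3 | 0.270 | 1.141 | 19 | 0.675 |

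In the last row, 156 × 0.141 = 22 is the number of extra participants needed to restore precision. The equivalent loss is 156 − 156/1.141 = 19.

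**3. The other reading of 0.6.** If 0.6 is the correlation across mixed entry days, the noise is already in the plan, and adding entry day raises R² to 0.36/(1 − f), where f is the share of baseline-score variance due to entry day. Exact power at 78 per arm, starting from 0.731:

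| f | 0 | 5% | 10% | 20% | 30% |
|---|---|---|---|---|---|
| Power with day added | 0.729 | 0.741 | 0.756 | 0.791 | 0.839 |

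The declines in step 2 correspond to f = 3k²/(81 + 3k²), which is 4%, 13% and 25%. The protocol gives no value for f.

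**4. Validity without the covariate.** In a simulation of 4,000 trials at 78 per arm, with f = 20% and no true effect, the model without entry day rejected in 5.0% of trials and the mean estimate was −0.01. The empirical SD of the estimate was 1.160 without entry day and 1.082 with it. The omission affects precision only.

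**The case against.** The strongest reply is that nothing here is wrong. Leaving a prognostic variable out of a randomized ANCOVA is an efficiency choice. The covariate list in 9.3 is worded as open, and a separate statistical analysis plan, not at hand, may already add this covariate. All of that stands, and it is why the point is a suggestion.

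The size is also open to challenge:

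- No passage gives the course of the VSS-SF over days 1 to 7 or links entry day to the 6-week score. The gain is therefore wholly assumed.
- A fall of 3 points per day means 18 points over six days, twice the assumed SD. The requirements to be symptomatic and to have documented nystagmus limit the spread.
- Sites differ in patient base (6.2), and ENT clinics recruit from subacute visits (6.7). The random site effect and diagnostic group may already absorb part of the variation.
- Onset must be known for eligibility, but the protocol does not show that its date is an analysis variable. Section 10.1 keeps screening lists outside REDCap.

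These points reduce the expected gain without removing the case for a covariate that costs so little. Site and diagnostic group need not capture variation in entry day within a site. Waiting for the data is not equivalent either, because a covariate chosen after unblinding is not prespecified.

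A reader might infer that the primary result would be biased, or that entry day explains the gap between 73% and 90% power. The simulation contradicts the first. The second is a separate question about how 0.6 was entered in 9.4. A reader might also extend the point to T25-FW, body sway, vHIT and DHI, but no calculation here supports a gain for those endpoints.

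**Conclusion.** The point holds as an optional improvement in efficiency. The protocol allows about a week's variation in when a 24-hour baseline score is taken and does not name that timing among the covariates. The treatment estimate and type I error remain valid without it.

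Under the assumptions of step 2, the cost of omission is about 2%, 7% or 14% in residual variance, or about 1, 3 or 6 points of power. It is near nil if entry days cluster or if existing model terms carry the same information. The calculation covers only noise in the baseline score. The shift in outcome timing is a further reason to include entry day, but its effect is not quantified.

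**What to change.** Before any unblinded analysis, name days from vertigo onset to baseline, as a continuous linear term, among the prespecified covariates of the primary ANCOVA. Confirm that the onset date established at eligibility screening is recorded in the analysis dataset, and add it if it is not.

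The cost is one degree of freedom. If entry day explains nothing, power at 78 per arm moves from 0.731 to 0.729. No visit, assessment or change in sample size is needed.

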#### 9.5. Pass/fail criteria

Pass: The study group randomized to the online vestibular rehabilitation scores mean  $\geq 3$  VSS-SF points lower compared with the standard care group at 6 weeks.

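### The normality fallback in section 9.3 can replace the primary ANCOVA with a model that does not give the mean difference in points on which section 9.5 decides pass or fail.

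*Protocol*

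**What the plan says.** Section 9.3 sets the primary method: "The primary outcome will be analyzed using analysis of covariance (ANCOVA) adjusting for baseline measurements", together with further predictors and a random effect for site. It also fixes the form of the result: "The primary endpoint results will be reported as the ANCOVA generated adjusted VSS-SF difference with 95% CI and p-value between the study arms". It supports the normal model by precedent: "The VSS-SF has previously been analyzed in a randomized trial assuming normality". The next sentence is the fallback: "If a clear deviation from normality is detected an ordinal logistic regression ANCOVA will be used for the primary outcome".

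Section 9.5 has a single criterion. The intervention group must have a mean at least 3 "VSS-SF points lower compared with the standard care group at 6 weeks". It names no model.

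Table 2 lists ANCOVA for the between-group mean VSS-SF difference, with 90% power. Section 9.4 calculates the sample size for a 3-point difference with an ANCOVA method. Neither mentions the ordinal model. Section 6.6.4 states that the statistical analyses are blinded.

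**The concern.** Success, power and the planned report are all expressed in points on the VSS-SF. The fallback changes the effect measure to an odds ratio and gives no success rule on that scale. If the fallback is used, the model called primary does not produce the quantity in 9.5, and the protocol does not say what takes its place.

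The investigation is described as pivotal and confirmatory (3.3). The later intended purpose (2.2) and release of the tool (section 13) depend on the primary endpoint. Which number decides should therefore not depend on the shape of the outcome data.

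**Working it through.** **1. The plan's own figure.** Inputs from 9.4: difference 3, SD 9, pre-post correlation 0.6, two-sided 5%, 90% power, 78 per arm, 15% dropout.
- Inflation: 156 / 0.85 = 183.5, so 184. This reproduces.
- ANCOVA with r = 0.6: residual SD = 9 × √(1 − 0.36) = 7.2. Then n = 2 × (1.960 + 1.282)² × 7.2² / 3² ≈ 121.1, so 122 per arm. A Shieh-type calculation gives 123.
- The stated 78 is reached if 0.6 is entered as R²: the Shieh-type power is 89.95% at 77 per arm and 90.3% at 78.

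That discrepancy is a separate matter. What counts here is that either reading is a calculation for a mean-difference ANCOVA, and none is given for an ordinal model.

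**2. Can the scores be close to normal?** Inputs: means and SDs from 9.4, scale range 0–60 from 6.3.
- Intervention: Φ(−8.1 / 7.4) = 13.7% below 0; mean − 2 SD = 8.1 − 14.8 = −6.7.
- Control: Φ(−11.5 / 9.9) = 12.3% below 0; mean − 2 SD = 11.5 − 19.8 = −8.3.

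A score that cannot be negative cannot be near normal with these moments.

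**3. How often would the trigger fire?** The protocol does not define the check, so this step rests on assumptions: Shapiro-Wilk at 5%; integer scores with the planning moments; three possible shapes; a roughly normal baseline (mean 25, SD 10); correlation with baseline of 0.6 or 0.7; 78 or 92 per arm; ANCOVA with arm and baseline; 2,000 runs per setting.

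| Assumed shape | Raw scores rejected in at least one arm | ANCOVA residuals rejected |
|---|---|---|
| Beta | 100% | 90–99% |
| Gamma | 100% | 99–100% |
| Left-censored normal | 100% | 34–69% |

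**4. Is the switch needed to protect the type I error?** With no difference between arms in the same simulations, the ANCOVA test of the mean difference rejected in 4.4% to 6.0% of runs over all shapes and both sample sizes. The Monte Carlo standard error is √(0.05 × 0.95 / 2000) ≈ 0.5 percentage points. The nominal 5% is approximately kept without switching.

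**5. Sections side by side.**

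| Item | ANCOVA | Ordinal model |
|---|---|---|
| Effect measure | Points on VSS-SF | Odds ratio |
| Pass rule | At least 3 points (9.5) | None stated |
| Power | 90% stated (9.4, Table 2) | None stated |

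**The case against.** Several points can be made for the plan.

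- **Likelihood.** A reader might infer that the switch is near certain. The documents do not support that. The moments come from chronic primary-care patients at three months, not acute vertigo at 6 weeks. The shapes and the Shapiro-Wilk trigger are assumptions, and a formal test also flags small departures at this sample size. The protocol notes that an earlier trial treated the scale as normal, and its planning figures come from that trial. What stands is that skew is likely, and that the trigger would almost surely fire if raw scores with these moments were tested formally.
- **An estimate remains.** A reader might infer that the 3-point criterion could not be evaluated at all. That goes too far. Section 9.5 needs only group means, 9.3 promises crude as well as adjusted analyses, and Table 2 lists the mean difference without condition. What is missing is a statement of which result would decide.
- **Selective choice and alpha.** A reader might infer a seriously inflated type I error from having two possible p-values. The rule names one replacement, and 6.6.4 states blinded analysis. In a separate simulation with 78 per arm and rank ANCOVA standing in for the ordinal model, following the rule gave 5.8% (gamma) and 4.9% (beta), against 5.6% and 4.5% for plain ANCOVA. Only taking the smaller p-value, which breaches the rule, raised it to 8.0% and 6.8%. The alpha concern is modest.
- **SAP detail.** How normality is judged may properly be left to the SAP, so the lack of a named test is not the point. The mismatch between the fallback and 9.5 is between two rules that this protocol states, and blinding does not resolve it.

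**Conclusion.** The point holds as a mismatch between stated rules. If 9.3 is followed and the fallback applies, the primary model gives an odds ratio, while 9.5 decides on a mean difference of 3 points, and the protocol does not say which result then governs. The stated 90% power does not carry over to the ordinal model.

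The fallback is a realistic prospect: 12–14% of a normal distribution with the planning moments lies below 0. The simulated firing rate is 100% on raw scores and 34% to 100% on residuals. Those rates depend on the planning moments applying to this population and on the assumed shapes and test.

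The switch gains no error control that ANCOVA lacks. The simulated model adjusted for baseline only, not for the full set of predictors and site. The change should be made, but the finding does not show that the trial would reach a wrong conclusion.

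**What to change.** In 9.3, delete the normality trigger. State that the ANCOVA adjusted mean difference at 6 weeks is the primary analysis whatever the distribution, with a robust or bootstrap 95% CI, and that the ordinal logistic model is always reported as a sensitivity analysis. In 9.5, state that this adjusted difference is the one compared with 3 points. Make the change before treatment allocation is joined to the outcome data.

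If the sponsor prefers to keep the fallback, the least that is needed is a statement that the adjusted mean difference with its CI is still reported and still governs 9.5.

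The cost is one sentence in 9.3 and a clause in 9.5; this change does not itself alter the sample size. The small downside is that an ordinal model may be more efficient under some skewed shapes. The rank-based stand-in showed no such gain in the two shapes tried (power 73% against 84% for ANCOVA under beta, 83% against 84% under gamma), and the ordinal result stays available as a sensitivity analysis.

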## 6.2. Measurements to minimize bias

Subjects will be block-randomized (random blocksize of 4, 6 and 8) 1:1 using site-specific randomization lists generated in R. Randomization will be performed by an independent statistician at Registercentrum Norr. As a precaution measure the lists will contain 4 times as many posts as the expected number of participants at each site. The treatment allocation will be open to the participants and to the site study coordinators, however blinded primary endpoint assessments at week 6 by study coordinators from surrounding sites will be performed as detailed below (section 6.7).

To minimize the risk for an increased effect of rehabilitation mediated by the increased motivation stemming from participating in a clinical trial (in both study arms) the study nurses will be instructed to try to avoid acting as “coaches” and instead concentrate on data collection at the contacts with the participants. This way the effect in the intervention arm will be isolated to the vestibular rehabilitation app, and the effect in the control arm will be isolated to mimic current clinical practice.

Sites will differ according to patient base (e.g., ENT outpatient clinics vs stroke wards). This will entail site mediated differences in participant characteristics. Bias stemming from these differences will be mitigated by including a random effect for site in the primary outcome analysis, and by site stratified randomization.

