## 9.12. Handling of imbalance of subjects per site

Randomization will be site-stratified. The primary effects analysis will include a random effect for site to control for influence from stratified randomization.

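### Randomisation is stratified by site, but several secondary and safety analyses state no site term, which makes the linear and rank tests conservative and costs some power where sites differ

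*Protocol*

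**What the plan says.** Protocol 6.2 has patients "block-randomized (random blocksize of 4, 6 and 8) 1:1 using site-specific randomization lists generated in R". It names ENT outpatient clinics and stroke wards as examples of differing patient bases and concludes: "This will entail site mediated differences in participant characteristics". The stated remedy is "including a random effect for site in the primary outcome analysis, and by site stratified randomization".

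Section 9.3 repeats this for the primary ANCOVA, with "inclusion of a random effect for site to control for influence from stratified randomization", and gives the mixed models for repeated secondary outcomes random effects for individual and site. Section 9.12 confines itself to the primary analysis: "The primary effects analysis will include a random effect for site to control for influence from stratified randomization".

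For other endpoints, 9.3 says "Ranked analysis of covariance (ANCOVA) will be used to evaluate intervention effects on T25-FW and VOR gain and saccades" and assigns sustained VSS-SF improvement to binary logistic regression. Crude and adjusted results will be reported, the latter "adjusting for baseline values of the studied outcome and the prespecified predictors sex, age, level of education, number of chronic diseases and baseline AVS etiology". Site is not in that list. Table 2 then fixes a method for each endpoint, in several rows plain ANCOVA, ranked ANCOVA or binary logistic regression.

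**The concern.** The protocol's reason for modelling site is the stratified randomisation. Every endpoint comes from that same randomisation, so the reason applies equally to steps, EQ-5D at 12 months, falls and BPPV, and no ground is given for treating them differently.

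When arms are balanced within site, differences between sites largely cancel out of the treatment contrast. A linear or rank model without site still counts those differences as error. Its standard error then exceeds the real sampling spread, the test rejects less often than its nominal level, and power is lost. Most of the affected rows in Table 2 list power as unknown, so the protocol shows no margin that would absorb the loss.

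**Working it through.** **1. Where site is stated**

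| Analysis | Section 9.3 | Table 2 | Site stated? |
|---|---|---|---|
| VSS-SF at 6 weeks (primary) | ANCOVA, random site effect | ANCOVA | Yes |
| DHI and EQ-5D to 3 months, body sway, compliance | Mixed model with site | Mixed models | Yes |
| EQ-5D at 12 months | Not named | ANCOVA | No |
| Total steps | Not named | ANCOVA | No |
| vHIT gain | Ranked ANCOVA | Ranked ANCOVA | No |
| Sustained VSS-SF improvement | Binary logistic | No row | No |
| BPPV | Not named | Binary logistic | No |
| T25-FW | Ranked ANCOVA | Mixed models | Depends on passage |
| Catch-up saccades | Ranked ANCOVA, or mixed logistic if treated as repeated binary | Binary logistic | Depends on passage |
| Falls/fractures | Mixed logistic if treated as repeated binary | Binary logistic | Depends on passage |

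**2. The one stated power figure in the affected set**

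Table 2 gives vHIT gain 0.52 (0.24) vs 0.69 (0.25), 50 per arm, power 99%.
- Difference 0.17; pooled SD √((0.24² + 0.25²)/2) = 0.245.
- Borrowing the correlation 0.6 from 9.4 (stated there for VSS-SF, so an assumption here), the residual SD is 0.245 × √(1 − 0.36) = 0.196.
- SE = 0.196 × √(2/50) = 0.0392, and 0.17/0.0392 = 4.34.
- Power = Φ(4.34 − 1.96) = 99.1%, so the figure is reproduced. Without a covariate it is 93.4%.

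**3. Effect of leaving site out (linear and rank models)**

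Let ρ be the share of outcome variance lying between sites after the other covariates. The protocol gives neither ρ nor the number of sites, so ρ is assumed to be 0.05, 0.10 or 0.20. With balance within site:
- model SE / true SE: k = 1/√(1 − ρ)
- true two-sided type I error = 2Φ(−1.960k)
- for 80% power computed on total variance, the expected z is 1.960 + 0.842 = 2.802
- power without site = Φ(0.842k); power with site = Φ(2.802k − 1.960)

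| ρ | k | Type I error | Power without site | Power with site | Loss (points) |
|---|---|---|---|---|---|
| 0 | 1.000 | 5.0% | 80.0% | 80.0% | 0 |
| 0.05 | 1.026 | 4.4% | 80.6% | 82.0% | 1.4 |
| 0.10 | 1.054 | 3.9% | 81.3% | 84.0% | 2.7 |
| 0.20 | 1.118 | 2.8% | 82.7% | 87.9% | 5.2 |

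The same formulas at 99% power (expected z 1.960 + 2.326 = 4.286) apply to vHIT gain. They give 99.2% vs 99.3% at ρ = 0.05 and 99.5% vs 99.8% at ρ = 0.20.

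**4. Simulation check**

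Ranked ANCOVA with permuted blocks of 4, 6 and 8 within site, ρ = 0.20, site numbers assumed:
- 156 patients, 11 sites: SE ratio 1.11 to 1.14, type I error 3.0%, power 88.8% without site vs 93.8% with it.
- 85 patients, 5 sites: SE ratio 1.12, type I error 3.1%, power 59.1% vs 67.7%.

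The second loss, 67.7 − 59.1 = 8.6 points, is larger because power there is lower. The formula agrees: (0.459 + 1.960)/1.118 = 2.164, and Φ((2.164 − 1.960) × 1.118) = 59.0%.

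**5. Logistic models**

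Assumed: control rate 30%, odds ratio 2.5 (log 0.92), 10 sites, site SD 0.5 or 1.0 on the logit scale.
- Mean log odds ratio without site: 0.89 or 0.77.
- SE without site 0.338 or 0.336; with site 0.361 or 0.387. The unadjusted SE is the smaller one, though 4% or 6% wider than that estimate's own spread.
- Power without vs with site: 76.2% vs 79.9%, or 63.1% vs 71.9%. At site SD 1.0 the site-adjusted test rejected in 6.9% of null trials (800 simulated), so the second gap overstates the gain.

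**The case against.** The strongest reply is that silence is not exclusion. No sentence bars site from any model. Table 2 carries bare labels: it says only ANCOVA for VSS-SF too, although 9.3 gives the primary model a site effect. The adjustment list in 9.3 names predictors, while site enters the primary and mixed models outside that list. A separate analysis plan could supply the term.

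Part of this stands: the labels and the list do not alone prove exclusion. But 6.2 and 9.12 tie the site effect specifically to the primary analysis. Section 9.11 treats this document as containing the original analysis plan, with relevant deviations reportable to the agency. Adding site later could therefore become a reportable change.

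Other points on that side are sound and limit the claim:
- A reader might infer that every non-primary endpoint lacks site. T25-FW falls under mixed models in Table 2, and repeated binary outcomes may fall under the mixed logistic rule in 9.3. Those are inconsistencies between passages, not clear omissions. Total steps, listed at two time points, could be argued the same way, although Table 2 names ANCOVA.
- A reader might expect VOR gain to suffer most because peripheral and stroke cases cluster by site. At the effect and power stated in Table 2 the loss is negligible, and adjustment for etiology takes up part of that clustering.
- A reader might extend the overly wide standard errors to the logistic models. There the main mechanism is the smaller, marginal odds ratio.

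**Conclusion.** The point holds as an inconsistency with a modest cost in efficiency. Site is not stated for EQ-5D at 12 months, total steps, vHIT gain, sustained VSS-SF improvement or BPPV. It is undetermined for T25-FW, catch-up saccades and falls/fractures.

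For linear and rank models near 80% power, the cost is about 1 to 5 points over an assumed residual between-site share of 5% to 20%, and more for weaker endpoints. It is zero if sites do not differ and smaller where etiology is adjusted for. The assumed shares and site numbers are not from the protocol.

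The documents do not support a reading that false positives are inflated: in the linear and rank models the error is conservative. Nor do they support one that the trial's main conclusion is at risk, since the primary analysis already includes site.

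**What to change.** - Extend 9.12 from the primary analysis to all between-arm secondary and safety analyses.
- Add site to the adjustment list in 9.3: a random intercept in the ANCOVA and logistic models, and site as a stratification factor in the ranked ANCOVA.
- Reconcile 9.3 with Table 2 on the method for T25-FW and for the repeated binary endpoints (catch-up saccades, falls/fractures), so that each has one model.
- State that the smallest sites will be pooled if a model with few events does not converge.

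The cost is a sentence in 9.12, a word in 9.3, corrected table entries and one term per model. The only real downside is possible non-convergence with sparse events, which the pooling rule covers. No change to data collection or sample size is needed.
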